### Item difficulty

We will assess the difficulty of each question by calculating the proportion of correct answers for each question. Item difficulty is important because it reveals whether an item is too easy or too hard. In either case, the item may add to the unreliability of the test because it does not aid in differentiating between participants. Wide range of difficulties allows a test to be used with both expert and novice groups.

The optimal item difficulty depends on the question-type. Nevertheless, scores per question by course participants should not fall below 0.1 or go above 0.9, as scores outside these parameters do not tend to provide additional information to distinguish the more knowledgeable participants from the less knowledgeable ones. Such items should either be revised or replaced.

We will analyse item difficulty only in the questions with two alternatives: true and false.

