The Fresno questionnaire was designed to assess all domains of EBP.[9] It begins with the presentation of two scenarios that suggest clinical uncertainty. Short answer questions about the clinical scenarios require the candidate to formulate a focused question, identify the most appropriate research design for answering the question, show knowledge of electronic database searching, identify issues important for determining the relevance and validity of a given research article, and discuss the magnitude and importance of research findings. Unlike multiple choice or true-false questions, the open ended questions require examinees to show higher order thinking in response to an authentic task. These questions are scored by using a standardised grading system.

Table 1 shows the psychometric properties of both questionnaires. It can be concluded that both are reliable and valid for detecting the effect of instruction in EBP. More time and expertise are required to grade the Fresno Test. [8] The multiple-choice format of the Berlin Questionnaire restricts assessment to EBP applied knowledge but also makes it more feasible to implement. Nevertheless, there is another important difference between them: whereas the Fresno test was designed to assess all domains of EBP, not all skills in EBP are captured by the Berlin test (i.e., formulation of question, competencies in searching), which is concentrated more on the handling of research information. In taking the Fresno Test, trainees perform realistic EBP tasks, demonstrating applied knowledge and skills. For this reason we have chosen for translation the Fresno test.

**Table 1 T1:** Properties of Berlin and Fresno test

**Test property**	**Measure used**	**Performance of Berlin test **[10]	**Performance of Fresno test **[9]
**Content validity **(test covers entire topic of interest)	Expert opinión	Expert opinion (five teachers in EBP)	Revisions based on experts' suggestions

**Inter-rater reliability **(degree to which 2 scorers rate a single performance similarly)	Inter-rater correlation	Total score 0.96 (IC 95%: 0.92–0.98)	Ranged from 0.76 to 0.98 for individual items, total scores 0.98

**Internal reliability **(degree to which all test questions on the test measure a single construct)	Cronbach's α average of all possible split half correlations	0.75	0.88

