**Item difficulty **(relative difficulty of each item)	% of candidates who answer achieve a passing score	Not given	Ranged from moderate (73%) to difficult (24%); no easy items

**Item discrimination **(ability of each item to discriminate between those with overall high scores and those with overall low scores)	Item discrimination index (ranges from -1.0 to 1.0)	Not given	Ranged from 0.41 to 0.86, no items had negative or weak discriminations

**Construct validity **(evidence that the test measures the construct it intends to)	Mean scores of experts and novices compared by *t *test	Significant difference, higher expert scores than novices	Significant difference, higher expert scores than novices

*Adaptation of Ramos et al[9]

The primary aim of the study is the translation of the Fresno questionnaire into Spanish and its subsequent validation to ensure the equivalence of the Spanish version against the English original.

The specific objectives are: (a) To translate the test into Spanish using the back translation method; (b) To assess the construct validity of the test comparing the scores achieved by tutors with formal methodological training in EBP, the scores of a group of family medicine residents before they have had any formal training in EBP, and finally the scores of a group of family medicine residents with intermediate experience (training) in EBP; (c) To assess the responsive validity (change in knowledge and skills) of the test after a short course in EBP carried out in a group of family medicine residents; (d) To assess the reliability of the test by measuring the internal reliability (degree to which all test questions on the test measure a single construct), the inter-rater reliability (degree to which two scorers rate a single performance similarly), the intra-rater reliability (degree to which onescorer rate a single performance similarly); (e) To assess the feasibility of implementation by reporting the time required administering the test and reporting the time required scoring the instrument.

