### Item discrimination

The single best measure of the effectiveness of an item is its ability to separate participants who vary in their degree of knowledge of the material tested, and their ability to use it. If one group of students has mastered the material and the other group had not, a larger portion of the former group should be expected to correctly answer a test item. Item discrimination is the difference in proportions for test takers answering correctly between those scoring in the upper 27% on total score and those scoring in the lower 27%. The following levels were used as a guideline for acceptable items: 0–24% unacceptable; 25%–39% good item; 40–100% excellent item.

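### The item-difficulty section promises a figure for each question, then limits it to true/false questions, so the graded open-ended items get none

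*Protocol article*

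**What the plan says.** The section on item difficulty begins with full coverage: "We will assess the difficulty of each question by calculating the proportion of correct answers for each question". It explains that an item which is too easy or too hard does not help to separate participants. It sets limits of 0.1 and 0.9 for course participants and says that items outside them should be revised or replaced. Its last sentence then narrows the scope: "We will analyse item difficulty only in the questions with two alternatives: true and false".

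The Background describes the instrument differently. It says of the format: "Unlike multiple choice or true-false questions, the open ended questions require examinees to show higher order thinking in response to an authentic task". On marking it adds: "These questions are scored by using a standardised grading system".

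Table 1, also in the Background, defines item difficulty as the percentage "of candidates who answer achieve a passing score". For the original Fresno test it reports: "Ranged from moderate (73%) to difficult (24%); no easy items".

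The section on item discrimination carries no true/false restriction. It defines the index as "the difference in proportions for test takers answering correctly between those scoring in the upper 27" per cent of total scores and those in the lower 27 per cent.

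**The concern.** The opening and closing sentences of the item-difficulty section cannot both be followed. If the closing sentence governs, eligibility depends on a feature that the Background says the open-ended questions do not have.

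At stake is the revise-or-replace rule. Translation can change how hard an item is, for example through an unclear scenario or an over-helpful prompt. The 0.1 to 0.9 limits are the plan's direct screen for that, and a graded item outside the restriction would never meet them. It would also have no Spanish figure to read beside the range reported for the original, although the study's primary aim is a Spanish version equivalent to the English one.

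**Working it through.** The plan states no sample size or item count for this analysis, so there is no figure of its own to reproduce. The check compares the sections and adds one bound.

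**1. Which items are eligible?** Two readings of the closing sentence are possible.
- *Literal (the question offers true and false as its options).* The article identifies no such question, and the Background contrasts the test with that format. No item described in the article qualifies.
- *Lenient (the answer is scored right or wrong).* The inter-rater reliability section separates qualitative items (kappa) from quantitative items (intra-class correlation), so some items may be scored in categories and could qualify. Items graded on a scale still do not.

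Graded items are left out on both readings. Their number is unknown.

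**2. Does the item format force the restriction?** No. Table 1 gives the original's difficulty as the percentage reaching a passing score, which turns a graded item into a pass/fail item. On the 0 to 1 scale the reported range is 0.24 to 0.73. It lies inside the limits, with a margin of 0.24 − 0.10 = 0.14 at the hard end and 0.90 − 0.73 = 0.17 at the easy end. The limits can therefore be applied to that measure.

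**3. Is item discrimination consistent with the restriction?** That index needs the proportion answering correctly in the top and bottom 27%. For a graded item, this requires a cut for what counts as correct. If a cut exists, difficulty can be computed for the same item and the restriction has no basis. If none exists, the index is undefined for that item.

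**4. How much do the unrestricted checks protect?** Assume that a cut is defined and that discrimination is computed in the same people as difficulty.
- Let p be the proportion passing an item. For p below 0.27, discrimination is largest when everyone who passes is in the top 27% and nobody in the bottom 27% passes. Hence D ≤ p / 0.27.
- The plan calls 0–24% unacceptable and 25–39% good. D is bound to be below 0.25 when p < 0.25 × 0.27 = 0.0675.
- By symmetry, for easy items D ≤ (1 − p) / 0.27, so D is bound to be below 0.25 when p > 1 − 0.0675 = 0.9325.
- At p = 0.10 the bound is 0.10 / 0.27 = 0.37, which falls in the good band.

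Discrimination therefore necessarily flags items below about 0.07 or above about 0.93. Items from about 0.07 to 0.10, and from 0.90 to about 0.93, breach the difficulty limits but can pass on discrimination. The corrected item-total correlation (threshold 0.30) may catch some of these, because an item that nearly everyone fails or passes varies little, but it does not measure difficulty.

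**The case against.** The strongest defence is that the closing sentence is loose English for items scored right or wrong. A condensed article may also leave the list of such items, and the marking rubric, to a fuller document. Part of this stands: the missing item counts and rubric are not a fault, and the use of kappa for qualitative items makes the lenient reading plausible. It does not remove the conflict. The restriction is a stated rule rather than an omitted detail, and under the lenient reading graded items are still excluded.

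A second defence is that difficulty is a supporting property. It is not among specific objectives (a) to (e), and no numerical comparison with the original's range is planned. That also stands. The Discussion says the original was validated in groups that were probably at the extremes of proficiency, so a different percentage passing would mix the effect of translation with that of population.

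A reader might go further than the document supports in four ways:
- *That no item at all will be assessed.* This is unproven, because some items may be scored right or wrong.
- *That a badly translated item would go unnoticed.* Item-total correlation and item discrimination are unrestricted and give partial cover.
- *That equivalence cannot be shown without the 24% to 73% comparison.* The plan does not rest equivalence on it.
- *That guessing makes the 0.1 limit useless on two-option items.* This presumes literal true/false items, which the article does not identify, answered by pure guessers. A misleading item can also score below chance, and an open answer marked right or wrong has no 50% guessing level.

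**Conclusion.** The point holds in a limited form. The item-difficulty section contradicts itself on scope. If its closing sentence is followed, graded items have no difficulty figure and are not tested against the 0.1 to 0.9 limits. This is certain from the wording on either reading. The number of items affected is not known.

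The practical loss is moderate. Some extreme items would be flagged by other checks, but the bands next to the limits (about 0.07 to 0.10 and 0.90 to 0.93) can escape the discrimination index. That bound assumes a pass cut and a common set of respondents, neither of which the article states. The same missing cut leaves it unclear how discrimination applies to graded items. The main construct-validity, responsiveness and reliability analyses are not affected.

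**What to change.** Make four changes to the text:
1. Delete the closing sentence of the item-difficulty section, so that its opening promise governs.
2. Define, for each item, a passing score taken from the grading system, in the manner of Table 1, and fix it before scoring starts.
3. Report the percentage passing for every item by group at pre-test (for experts, their single administration), and apply the 0.1 to 0.9 limits to all items.
4. State that the same cut defines a correct answer in the item discrimination index.

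Add a sentence saying that any comparison with the original's 24% to 73% is descriptive because the populations differ. If the restriction is kept instead, list the eligible items and state that difficulty is not assessed for the rest.

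The cost is a few lines of wording and a little extra tabulation. No further data are needed.

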### Item discrimination

The single best measure of the effectiveness of an item is its ability to separate participants who vary in their degree of knowledge of the material tested, and their ability to use it. If one group of students has mastered the material and the other group had not, a larger portion of the former group should be expected to correctly answer a test item. Item discrimination is the difference in proportions for test takers answering correctly between those scoring in the upper 27% on total score and those scoring in the lower 27%. The following levels were used as a guideline for acceptable items: 0–24% unacceptable; 25%–39% good item; 40–100% excellent item.

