### Setting and context

The setting of the study will be the Primary Care Teaching Units in Catalonia (PCTU). At the beginning of the Family Medicine residence program (which longs four years) the medical residents are enrolled into a PCTU. Each PCTU comprises several health centers in a defined geographical area. There are seventeen PCTU in Catalonia.

The number of medical residents in each PCTU ranged from 2 to 52 in 2007. In the year 2007 there were 202 residents in their second year of training.

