### Internal consistency

Internal consistency refers to the extent to which individual items of the instrument are consistent to one another and reflect an underlying scheme or construct. For internal consistency reliability, two measures will used: Cronbach's alpha and corrected item-total correlations.

Cronbach's alpha coefficient is used to evaluate the internal consistency between the questionnaire elements. Cronbach's alpha coefficient measures how well a set of items (or variables) measures a single uni-dimensional latent construct. Achievable values for Cronbach's alpha range from 0 (signifying no correlation) to 1 (indicating identical results). When data have a multidimensional structure, Cronbach's alpha will usually be low. Technically speaking, Cronbach's alpha is not a statistical test – it is a coefficient of reliability (or consistency).[18]

The reliability of an instrument has implications for whether it is suitable for application in group or individual evaluation. For the evaluation of individuals high levels of reliability, above 0.90, have been recommended. For group comparisons, levels over 0.70 are recommended. In the present study, values greater than 0.70 will be considered evidence of internal consistency.[19]

Pearson's correlation coefficient will be also calculated to assess the relation between an individual item and the instrument as a whole omitting that item (corrected item total correlation) to identify items contributing to a low reliability. Corrected item-total correlations indicate the extent to which each item relates to the construct measured by the total score. Correcting the total score by removing the item of interest prevents spuriously high values due to item overlap; values greater than 0.30 will be considered evidence of internal consistency. [20]

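### Item discrimination is computed on a total score that still contains the item, so the index is biased upwards and can disagree with the corrected item-total correlation

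*Protocol article*

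**What the plan says.** The Item discrimination section defines the index as the difference in proportion correct between "those scoring in the upper 27% on total score and those scoring in the lower 27" per cent. The guideline bands are "0–24% unacceptable; 25%–39% good item; 40–100% excellent item". Nothing in the section takes the judged item out of the total before the groups are formed.

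The Internal consistency section does take it out for the neighbouring statistic, the corrected item-total correlation, and gives the reason: "Correcting the total score by removing the item of interest prevents spuriously high values due to item overlap". That correlation is read against a threshold of 0.30. For Cronbach's alpha, "values greater than 0.70 will be considered evidence of internal consistency".

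Table 1 in the Background gives alpha 0.88 for the English test. Of its item discrimination it reports: "Ranged from 0.41 to 0.86, no items had negative or weak discriminations".

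**The concern.** Answering an item correctly raises the total and so helps place a person in the upper group. The index is therefore pushed above zero by construction, even for an item that has nothing to do with the rest of the test. The article recognises this bias for one item statistic and leaves it in the next, where fixed bands are applied.

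The study validates a translation, so an item that stopped working in Spanish is what the item analysis should reveal. An index biased upwards makes that harder to see. The bias also differs between items: the larger an item's share of the total score variance, the larger the artefact, so 25% does not mean the same thing for every item.

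**Working it through.** The article states no error rate or sample size for this rule, so there is no figure of its own to reproduce.

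**Inputs from the article**
- The index definition and bands (Item discrimination).
- Alpha above 0.70 as the criterion (Internal consistency) and 0.88 for the English test (Table 1).
- On the number of test takers, only the size of the pool: "In the year 2007 there were 202 residents in their second year of training".

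**Assumptions**
- 12 to 20 items, with 7 and 10 as shorter tests.
- n = 200, with 60 and 100 as smaller samples.
- The judged item is scored right/wrong with p = 0.5 correct, has the same score SD as the others, and is unrelated to them.
- Alpha is that of the other k − 1 items.

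**Step 1, expected index for an unrelated item.** Take the SD of each item as 1.
- Mean inter-item correlation of the others: r̄ = alpha / [(k − 1) − alpha(k − 2)]
- Item-total correlation from overlap alone: r = 1 / √[1 + (k − 1) + (k − 1)(k − 2) r̄]
- Expected index: E[D] = 2 × 1.2246 × r × √(p(1 − p)), where 1.2246 is the normal mean of the upper 27%

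For 12 items and alpha 0.88: r̄ = 0.88 / (11 − 8.8) = 0.40; r = 1 / √(1 + 11 + 44) = 1 / √56 = 0.134; E[D] = 2 × 1.2246 × 0.134 × 0.5 = 0.164.

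**Step 2, chance of reaching 25% at n = 200.** Each group has 0.27 × 200 = 54 people, so SE(D) is about √(2 × 0.25 / 54) = 0.096. The normal approximation is P = 1 − Φ[(0.25 − E[D]) / 0.096].

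| Items | Alpha | r̄ | r | E[D] | P, normal approx. | P, simulated |
|---|---|---|---|---|---|---|
| 12 | 0.70 | 0.17 | 0.179 | 0.219 | 37% | 36% |
| 12 | 0.88 | 0.40 | 0.134 | 0.164 | 19% | 18% |
| 20 | 0.70 | 0.11 | 0.132 | 0.162 | 18% | 16% |
| 20 | 0.88 | 0.28 | 0.093 | 0.114 | 8% | 8% |

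The simulated column treats the other items as continuous. When they too are right/wrong, tied totals blunt the split slightly: the mean index is about 0.10 to 0.20, and P runs from about 7% (20 items, alpha 0.88) to 31% (12 items, alpha 0.70).

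**Step 3, item removed from the total.** E[D] = 0 and P = 1 − Φ(0.25 / 0.096), about 0.5%. Simulation gives under 1% at n = 200, 3% to 5% at n = 100 and about 10% to 12% at n = 60.

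**Step 4, sensitivity with the item left in** (simulated, other items continuous)
- Shorter test, n = 200: 10 items, 50% (alpha 0.70) and 27% (0.88); 7 items, 78% and 52%.
- Smaller sample, 12 items, n = 60: 52% (alpha 0.70) and 37% (0.88).
- Harder item, p = 0.25, 12 items, n = 200: 25% (alpha 0.70) and 9% (0.88).
- Item spread relative to the others, 12 items, alpha 0.88, n = 200: half the SD, 3%; 1.5 times, 49%; twice, 79%.

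**Step 5, the article's other item check.** In simulations of an unrelated item (7 to 20 items, alpha 0 to 0.88, and a double-weight item with 12 items), the item reached 25% on the uncorrected index and also exceeded 0.30 on the corrected item-total correlation in about 1% of runs at n = 60, 0.1% to 0.2% at n = 100 and none of 3,000 at n = 200.

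**The case against.** The strongest reply is that the protection already exists. The corrected item-total correlation is computed specifically to find weak items, and by Step 5 almost no unrelated item would pass both checks. This stands, and it limits the consequence. What remains is that the two statistics can give opposite verdicts on the same item, and the article does not say which one prevails.

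Second, the bands are called a guideline, and no action is attached to them; revision or replacement is mentioned only under Item difficulty. This also stands. They are still offered as levels of acceptability, and the same section presents discrimination as the best single measure of an item.

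Third, the total-score form matches the way Table 1 describes discrimination for the English test, and equivalence with that test is the primary aim. That is a good reason to report the conventional index, but not to read the bands on it alone.

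Fourth, the size rests on inputs that the article does not give. The test has open-ended questions, and "These questions are scored by using a standardised grading system"; a wholly right/wrong test is a simplification. The direction of the bias does not depend on this, but its size does.

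A reader might infer that items with no discrimination are rated good most of the time. The article does not support that. It would take items that are nearly independent, a test of about 7 items, a small sample combined with about 10 to 12 items and alpha near 0.70, or an item weighted well above the rest. Near-zero alpha conflicts with the 0.88 of the English test and with the criterion of 0.70, and the other conditions are not stated anywhere.

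**Conclusion.** The point holds and is minor. The discrimination index carries an overlap bias that the article itself recognises and removes elsewhere. Under the main assumptions (12 to 20 equally weighted right/wrong items, 50% correct, alpha 0.70 to 0.88, n = 200), an item that discriminates nothing reaches the good band in about 7% to 31% of samples instead of under 1%. The rate is higher for shorter tests, smaller samples or heavily weighted items, and lower for harder items or items with little spread. In the main range the mean index of such an item, about 0.10 to 0.20, still lies in the unacceptable band.

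It would be tempting to conclude that badly translated items will go undetected. The documents do not support this, because the corrected item-total correlation would flag nearly all of them. The supported conclusion is that the reported discrimination is overstated and that the two item statistics may conflict.

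**What to change.** In the Item discrimination section, state that for each item the upper and lower 27% groups are formed on the total score omitting that item, as is already done for the item-total correlation, and that the guideline bands are read on this corrected index. Report the conventional uncorrected index beside it, as description only, for comparison with the English range of 0.41 to 0.86.

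The cost is one sentence of text and one re-sort per item, with no new data. The downside is that the corrected indices will be lower and are not themselves comparable with the published English range, which is why both should be shown.
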